### Statistical plan

The Shapiro–Wilk normality test will be used to test the normal distribution of continuous variables which will be expressed as mean ± standard deviation or median (25th, 75th percentile), as appropriate. Categorical variables will be expressed as frequency and percentage. When comparing data between recovered COVID-19 patients and healthy controls, chi-square testing or Fisher’s exact test will be used for categorical variables and two sample t-test or Mann–Whitney U test used for continuous variables, as appropriate. Functional performance, biomarker results and imaging metrics indicative of organ injury will be compared across groups of symptom severity (none, mild, moderate and severe) within the recovered COVID-19 patients using a one-way analysis of variance with *post hoc* pairwise comparisons by either Tukey’s or Games-Howell tests, depending on equality of variances. Pearson correlation analyses will evaluate relationships between MRI measures of tissue injury and functional performance metrics. Univariable Cox proportional regression of clinical outcome will be performed in all serum and imaging parameters. In the multivariable Cox proportional hazard analysis, all non-collinear parameters of interest with univariable *p*-value < 0.2 will independently test for their association with composite outcome after adjustment for baseline risk. A *p* value less than 0.05 will be considered significant for all tests.

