**Methods:**

A multicenter, observational study of 215 vaccine-naïve patients with clinically recovered COVID-19, studied at 3–6 months following infection, and 133 healthy volunteers without prior SARS-CoV-2 infection. Patients with recovered COVID-19 were screened for long COVID related symptoms and their impact on daily living. Multi-organ, multi-parametric magnetic resonance imaging (MRI) and circulating biomarkers were acquired to document sub-clinical organ pathology. All participants underwent pulmonary function, aerobic endurance (6 min walk test), cognition testing and olfaction assessment. Clinical outcomes were collected up to 1 year from infection. The primary objective of this study is to identify associations between organ injury and disability in patients with long-COVID symptoms in comparison to controls. As a secondary objective, imaging and circulating biomarkers with the potential to exacerbate cardiovascular health were characterized.

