**Figure 1 fig1:**
[figure not shown]
Schema of study design. Upper panel depicts recruitment of patients with recovered COVID-19 and healthy controls without prior COVID-19. Middle panel depicts functional testing, blood collection and magnetic resonance imaging for all participants. Functional testing included Brief Smell Identification Testing (B-SIT), 6 min walk testing, cognitive testing on a tablet with NIH toolbox and spirometry. Bottom panel depicts collection of clinical outcomes at 12 months. CBC, complete blood count; AST, aspartate aminotransferase; ALT, alanine aminotransferase; LDH, lactate dehydrogenase; GGT, gamma-glutamyl transferase; LVEF, left ventricular ejection fraction; DTI, diffusion tensor imaging.

A detailed assessment of relevant medical history and medication use was achieved through direct questioning and a review of health records. In patients with recovered COVID-19, data on the timing and duration of illness, the need for hospitalization and transfer to intensive care were recorded.

At the time of study-related functional assessments and MRI, patients with recovered COVID-19 were screened for the presence of long COVID related symptoms including fatigue, cognitive impairment, shortness of breath, chest pain and palpitations using a standardized questionnaire. Additionally, patients rated the overall impact of these symptoms on their daily activities using a 5-point scale ranging from 1 (no limitations) to 5 (severely limited).

Blood pressure, heart rate and oxygen saturation were measured on all participants and blood work was performed to assess for circulating biomarkers of inflammation (c-reactive protein, white blood cell count with differential and d-dimer), end organ damage (high sensitivity cardiac troponin I, b-type natriuretic peptide, creatinine and hepatic enzymes) and cardiometabolic profile (glucose, insulin and lipid profile). Blood biospecimens were also stored in a research biobank (Canadian BioSample Repository) for future analysis.

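### The provision for unequal variances reaches only the post hoc tests; the overall four-group test stays an unqualified one-way ANOVA, whose p value can then err in either direction

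*Protocol article*

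**What the plan says.** Under Statistical plan, the organ-injury metrics "will be compared across groups of symptom severity (none, mild, moderate and severe"). The overall test for this is named in the same sentence: it is done "within the recovered COVID-19 patients using a one-way analysis of variance with" follow-up tests of the pairs. The choice for the pairs is Tukey's or "Games-Howell tests, depending on equality of variances". No Welch or other unequal-variance form of the overall test is named. The same section adds that a p "value less than 0.05 will be considered significant for all tests".

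The Abstract gives the number of patients to be divided: "observational study of 215 vaccine-naïve patients with clinically recovered COVID-19". Patients rate the impact of symptoms on a "5-point scale ranging from 1 (no limitations) to 5 (severely limited"), but no count and no outcome SD is reported for any severity group. Table 3 describes the recovered patients only as a whole.

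**The concern.** The plan foresees unequal variances and supplies a remedy for one half of a two-step procedure. The classical F test pools the within-group variances. When group sizes and variances both differ, the pooled value is dominated by the larger groups, and the F ratio no longer centres on 1 under the null. The direction depends on the pattern: the test rejects too often if small groups have the larger spread, and too seldom if large groups do.

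This matters because the ANOVA is the planned comparison across symptom severity within patients. It bears directly on the hypothesis in the Introduction that tissue injury on MRI goes with reported disability. It is applied to the many metrics in Table 1, each judged at 0.05. Severity groups are observed and not allocated, so nothing in the design makes them equal in size.

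**Working it through.** **Inputs from the article.** Four groups, 215 patients in total, significance level 0.05, overall test one-way ANOVA.

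**Inputs assumed.** Group sizes, and SDs in relative units with a largest-to-smallest ratio of mainly 1.5 to 2. Data are normal and, for error rates, true means are equal.

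**Step 1: why the direction depends on the pattern.** With equal true means and k = 4 groups of size nᵢ and variance σᵢ²:

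- E(MS between) = Σ(1 − nᵢ/N)σᵢ² / (k − 1)
- E(MS within) = Σ(nᵢ − 1)σᵢ² / (N − k)

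With SDs 1:1:1:2 and N = 215:

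- Sizes 90/70/40/15 (smallest group most variable): between = (0.581 + 0.674 + 0.814 + 4 × 0.930)/3 = 1.93; within = (89 + 69 + 39 + 4 × 14)/211 = 1.20; ratio 1.61.
- Sizes 15/30/70/100 (largest group most variable): between = (0.930 + 0.860 + 0.674 + 4 × 0.535)/3 = 1.53; within = (14 + 29 + 69 + 4 × 99)/211 = 2.41; ratio 0.64.
- Sizes 54/54/54/53: between = (3 × 0.749 + 4 × 0.753)/3 = 1.75; within = (3 × 53 + 4 × 52)/211 = 1.74; ratio 1.01.

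A ratio above 1 makes the test too liberal, and one below 1 too strict. Near-equal sizes almost remove the shift, although the shape of the null distribution still changes a little.

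**Step 2: the plan's own figure.** With equal SDs, 20,000 simulated null data sets per layout gave a classical F error of 4.8–5.3%. This is the stated 5% within simulation error.

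**Step 3: unequal SDs.** Type I error at nominal 5%:

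| Pattern (assumed) | Classical F |
|---|---|
| Smallest group most variable, SD ratio 1.5 (sizes 80/65/45/25 to 110/60/30/15; also 70/70/50/25 and 60/80/60/15) | 8.3–11.4% |
| Same layouts, SD ratio 2 | 10.5–18.0% |
| Near-equal groups 54/54/54/53, SD ratio up to 2 | 5.2–6.9% |
| Sizes 60/60/55/40, SDs 1:1:1.25:1.5 and 1:1:1.5:2 | 6.6% and 9.1% |
| Larger groups more variable | about 1–3% |

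Across the layouts simulated, Welch's F stayed at about 5% (4.6–5.3%). It weights each group mean by wᵢ = nᵢ/sᵢ² in place of the pooled variance. The chance that Games-Howell rejects any pair, without a preceding overall test, was 4.1–5.3%.

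**Step 4: how the two steps can disagree.** With sizes 70/75/50/20 and SDs 1:1:1.5:2, 10.4% of null data sets gave a significant ANOVA with no significant Games-Howell pair.

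**Step 5: power in the reverse pattern.** SDs 2:1.5:1:1, true shift of 0.7 (in units of the smallest group's SD) in the smallest group:

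- Sizes 70/75/50/20: classical F 25%, Welch 64%.
- Sizes 90/65/40/20: classical F 20%, Welch 64%.

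**Step 6: price of Welch when variances are equal.** Power was 70.2% for the classical F against 68.0% for Welch in one comparison, and 69.4% against 67.4% in another: about 2 percentage points.

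**The case against.** The strongest reply is that the plan's conclusions about which groups differ come from the pairs, and the pairs are protected. The full sequence was simulated with 6,000 null data sets per scenario: ANOVA first, then Tukey or Games-Howell chosen by a median-centred Levene test (an assumption, since the article names no check). The chance of any false pairwise claim after a significant F was 6.5% and 4.7% with sizes 70/75/50/20, 5.8% and 3.8% with 90/65/40/20, and 4.5% and 3.4% with 60/60/55/40. The second figure in each pair is for the wider SD spread. This stands. A reader might infer that the inflated overall test carries through to false statements about particular symptom groups; it does so only slightly, if at all. What remains is the overall p value, which will be read against 0.05 in its own right.

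The second reply is that the sizes and SDs are not in the article. This also stands. A reader might infer that unequal groups alone push the error to two or three times nominal, or that the most affected group will be the smallest and most variable. The article supports neither. Unequal size is not enough, since the smaller groups must also have the larger spread. Recruitment partly by self-referral, described under Participant selection, gives no basis for predicting the symptom split.

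The third reply is that the article does not use the word classical, and that a fuller analysis plan may name Welch's test. That is possible. But the article does state the rule, and attaches the variance condition to the post hoc tests alone; the unqualified term ordinarily means the equal-variance F test.

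**Conclusion.** The point holds as an inconsistency in the stated rule: unequal variances are anticipated, but the overall test is not adapted to them. Its size is conditional. Under assumed group sizes and an SD ratio of 1.5 to 2 with 215 patients, the overall error is roughly 8–18% if the smallest of clearly unequal groups is the most variable, about 5–9% with more even groups, and about 1–3% if the largest group is the most variable.

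In the first pattern the harm is a misleading overall p value, not unreliable pairs. In the last, real differences are missed if post hoc tests are run only after a significant ANOVA, which is common practice but is not stated in the article. The documents cannot show which pattern will arise, and it may differ between metrics. Since Welch's test holds about 5% in all of them, the case for changing does not depend on predicting it.

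**What to change.** In the Statistical plan, name Welch's one-way ANOVA as the overall test across symptom-severity groups, paired with Games-Howell. At minimum this should apply whenever variances are judged unequal. Preferably it should apply throughout, so that the choice of test does not rest on a preliminary variance check. It needs no new data and is a standard software option. The cost is the loss of about 2 percentage points of power when variances are equal. If a fuller analysis plan already specifies Welch's test, aligning the article's wording with it is enough.

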## Abstract

**Introduction:**

Short-term clinical outcomes from SARS-CoV-2 infection are generally favorable. However, 15–20% of patients report persistent symptoms of at least 12 weeks duration, often referred to as long COVID. Population studies have also demonstrated an increased risk of incident diabetes and cardiovascular disease at 12 months following infection. While imaging studies have identified multi-organ injury patterns in patients with recovered COVID-19, their respective contributions to the disability and morbidity of long COVID is unclear.

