The prevailing etiologic mechanisms proposed for long COVID include immune dysregulation, autoimmunity and immune imprinting, endothelial dysfunction and thrombosis, impaired neurological signaling and effects on the host microbiome (10). However, knowledge on pathogenesis remains limited and there is an important unmet need for rigorous preclinical and clinical studies in long COVID. Given the systemic (i.e., multi-organ) nature of both acute phase COVID-19 illness and long COVID, knowledge has been gained from whole body imaging. Magnetic resonance imaging (MRI) is a safe (non-ionizing radiation), non-invasive imaging technique that provides detailed information on tissue changes including injury. MRI has been used as an alternative to computed tomography for the characterization of pulmonary disease following severe COVID-19 pneumonia (11). MRI derived measures of visceral adipose tissue and liver fat are also strongly associated with risk of hospitalization from COVID-19 independent of body mass index (12). Whole body MRI-based studies of patients with recovered COVID-19 have identified subclinical multi-organ involvement (13–15). In an MRI study of 201 patients with long COVID, mean age 45 years, organ damage was identified in 70%, including the pancreas in 45%, liver in 29% and heart in 24% (14). In this study, MRI evidence of organ impairment was defined as a non-contrast T1 time (longitudinal relaxation time) greater than normal reference values. Several cardiac MRI based studies of patients with recovered COVID-19 have found evidence of subclinical myocardial inflammation (16–18), however, the clinical significance of this finding is not well established.

We undertook a multicenter, prospective study of patients in Alberta with recovered COVID-19 from October 2020 to August 2021 to characterize symptom burden, functional impairment and end-organ damage by MRI. We hypothesized that the extent of tissue injury on MRI would be associated with patient reported disability and objective measures of functional performance.

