Our primary objective was to comprehensively apply multi-system MRI to assess the presence and extent of organ injury (heart, lungs, brain, abdominal viscera and skeletal muscle) among patients with recovered COVID-19 and compare these findings between patients with moderate to severe symptoms, minimal symptoms, and healthy controls without prior infection. As a secondary objective, we also sought to characterize imaging and circulating biomarkers with the potential to exacerbate cardiovascular health. Additionally, we incorporated opportunistic supplementary studies to explore the impact of COVID-19 on energy metabolism and patient’s perspectives.

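### Organ metrics are tested one at a time against function and symptom severity, so the plan can show marginal associations but not any one organ's own contribution

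*Protocol article*

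**What the plan says.** Two analyses in the Statistical plan link organ metrics to how patients feel and perform. In the first, functional, biomarker and imaging measures are compared across four symptom-severity groups "using a one-way analysis of variance with" post hoc pairwise tests. In the second, "Pearson correlation analyses will evaluate relationships between MRI measures of tissue injury and functional performance metrics". Neither includes a second organ or a covariate.

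Multivariable modelling appears once in that section. It follows the step "Univariable Cox proportional regression of clinical outcome will be performed in all serum and imaging parameters" and is a Cox model for the composite clinical outcome, with a collinearity screen and adjustment for baseline risk.

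The abstract's Introduction says of the organ injury patterns that "their respective contributions to the disability and morbidity of long COVID is unclear". The abstract's Methods gives the objective: "The primary objective of this study is to identify associations between organ injury and disability in patients with long-COVID symptoms in comparison to controls". The main Introduction adds: "We hypothesized that the extent of tissue injury on MRI would be associated with patient reported disability and objective measures of functional performance". The Discussion sets the primary goal as better knowledge of the mechanisms behind disability. Table 1 lists the 6-minute walk as the functional measure for lung, heart and skeletal muscle.

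**The concern.** A pairwise correlation mixes an organ's own relation to the outcome with whatever it shares with other organs. If lung injury shortens the walk and heart metrics tend to be abnormal in the same patients, the heart metric correlates with walk distance even if it adds nothing. Three organs share this one outcome, so the plan will correlate it with each in turn and cannot tell driver from bystander. Adjusting each pair for age and sex would not solve this, because the missing variable is the other organ.

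The multivariable Cox model does not help, because its outcome is clinical events and not function or disability. A reader who uses the results to pick mechanisms or treatment targets could be pointed to the wrong organ.

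**Working it through.** **Inputs from the protocol.** There are 215 recovered patients (abstract; Table 3) and a significance level of 0.05 for every test (Statistical plan). Sidedness is not stated, so I take two-sided. The protocol gives no figure to reproduce: the target of 200 patients and 100 controls was set empirically, without an effect size or power.

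**Assumptions.** The protocol gives no correlation between organ metrics and none between a metric and function. I assume that all 215 patients have complete data, that only the lung metric drives walk distance with r = 0.35, and that the lung, heart and muscle metrics correlate equally (ρ) with one another, for ρ from 0.1 to 0.5.

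**Step 1: one bystander.** An organ with no effect of its own has a marginal correlation with walk distance of 0.35 × ρ. Fisher's z gives the chance of significance, approximately 1 − Φ(1.96 − atanh(r) × √(215 − 3)), plus a small lower tail. At ρ = 0.4, r = 0.35 × 0.4 = 0.14, atanh(0.14) × √212 = 2.05, and the chance is 54%.

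**Step 2: heart or muscle.** The chance that at least one of the two is falsely significant comes from simulation with 4,000 runs, where the standard error is at most √(0.5 × 0.5 / 4000) = 0.8 percentage points. The joint model is ordinary least squares with all three metrics entered together.

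| ρ | Marginal r of bystander | One bystander, Pearson | Heart or muscle, Pearson | Heart or muscle, joint model |
|---|---|---|---|---|
| 0.1 | 0.035 | 8% | 16% | about 10% |
| 0.2 | 0.070 | 18% | 31% | about 10% |
| 0.3 | 0.105 | 34% | 53% | about 10% |
| 0.4 | 0.140 | 54% | 73% | about 10% |
| 0.5 | 0.175 | 73% | 86% | about 10% |

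The 10% is what two true-null tests at 5% produce: 1 − 0.95² = 9.75%. Power for lung in the joint model stays above 99%.

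**Step 3: sensitivity to the driver's strength.** For a single bystander, a driver correlation of 0.2 gives 9% at ρ = 0.2 and 22% at ρ = 0.4. A driver correlation of 0.3 gives 14% and 42%. In the two-organ simulation at 0.3, mutual adjustment brings the rate back to about 5%.

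**Step 4: price of the joint model.** With three equally correlated metrics the variance inflation is (1 + ρ)/[(1 − ρ)(1 + 2ρ)]. At ρ = 0.5 this is 1.5/(0.5 × 2) = 1.5, so intervals are √1.5 = 1.22 times as wide as with uncorrelated metrics. Three predictors leave 215/3 ≈ 72 patients each, and six leave 215/6 ≈ 36. Entering all 13 MRI entries of Table 1 would leave 16.5, which is a reason to fix one lead metric per organ.

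**The case against.** The best reply is that the study promises only associations. The abstract's phrase about respective contributions is background. The stated objective is to identify associations, and the main Introduction describes it as to "assess the presence and extent of organ injury (heart, lungs, brain, abdominal viscera and skeletal muscle) among patients with recovered COVID-19" and to compare groups. Pairwise tests can meet that objective. This stands, and it limits the point: the planned tests are valid for marginal associations. It does not answer the Discussion's goal of understanding mechanisms, for which marginal associations are not enough.

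A second reply is that this is a condensed article and a full analysis plan may add a joint model. That is possible. But the article does specify multivariable modelling with a collinearity screen for clinical events, and names only one-metric tests for function and symptoms.

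A third reply is that the correlations are assumed. That also stands. The nearest evidence is under Sample size calculation: a cited study of 54 patients found cardiac, renal and hepatic T1 and brain T2* all related to circulating inflammation. This fits a shared driver but does not prove one, and it does not cover lung or muscle.

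A reader might go further and infer that the hypothesis has no test because no overall injury score is defined. The text does not support this. The hypothesis does not speak of overall injury, and the objective and Table 1 are laid out organ by organ. On that reading the ANOVA and Pearson tests do address it.

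Nor does it follow that an averaged multi-organ score should lead. With six organs each at r = 0.10, such a score has 62% to 84% power at ρ from 0.3 down to 0.1. The chance that at least one Bonferroni-adjusted test is positive is about 44% to 50%. But if one organ drives the outcome at r = 0.20 and ρ = 0.2, the score correlates (1 + 5 × 0.2) × 0.20/√(6 + 30 × 0.2) = 0.115 with it. That gives 39% power, against 84% for that organ's own test (62% after Bonferroni). The cited 201-patient study, in which only myocardial T1 was related to severe symptoms or disability, looks more like the second case.

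**Conclusion.** The point holds as a limit on what the analysis can show. As written, the plan can report which organ metrics are associated with function or symptom severity. It cannot separate one organ's own contribution from that of a correlated organ.

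Under the stated assumptions, false attribution to heart or muscle runs from about 16% to 86%, against about 10% in a joint model. At ρ = 0.1 the excess is small. It becomes serious from about ρ = 0.2 upward if the driver is moderately strong, and it shrinks with a weaker driver. The range illustrates the problem and does not predict this study's result. The change is worth making because it is cheap and the planned analyses are still described in the future tense, but the pairwise tests are not invalid for their own purpose.

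**What to change.** In the Statistical plan:

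- Prespecify one lead MRI metric each for lung, heart and skeletal muscle, chosen before the associations are examined.
- Fit one linear model for 6-minute walk distance in the recovered patients with the three lead metrics entered together.
- Fit a corresponding joint model of the lead organ metrics for the 1-to-5 rating of impact on daily activities, for example proportional odds.
- Report partial effects with 95% confidence intervals as the evidence on each organ's contribution.
- Keep the pairwise Pearson and ANOVA results, labelled as descriptive marginal associations.

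The cost is some wording and two models on data already collected. Intervals will be somewhat wider (up to 1.22 times in the example above), and patients missing one organ's metric must be imputed or are lost. Partial effects remain observational associations and should be described as such. If the joint models are not adopted, the report should speak only of marginal associations and draw no conclusion about which organ is responsible.

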*Skeletal Muscle*: Skeletal muscle T1 and fat content (intermuscular, intramuscular, and subcutaneous) was measured using a muscle-specific variant of the SR-CSE approach. Typical image parameters include 5 axial slices (centered 17 cm superior to the distal head of the femur) with a 3.5 mm thickness (12.5 mm gap), [2.51 3.51 4.51 4.78 5.78 6.78] ms echo times, 9.0 ms repetition time, 30° flip angle, rate 2 parallel imaging (GRAPPA) for a 41 s acquisition. A custom machine learning segmentation approach will be used to identify subcutaneous fat, intermuscular fat, muscle and bone regions. Calculated parameters included volumes of subcutaneous fat, muscle, intermuscular fat, intramuscular fat (fat content in the muscle region), muscle T1 and muscle T2* (from the muscle region).

*Lungs*: Lung images were acquired using a custom non-Cartesian ultrashort TE (TE = 70 μs) yarnball *k*-space trajectory with free-breathing acquisitions (31). Free-breathing data collection was completed in 120 s with reconstruction of 2 mm × 2 mm × 2 mm resolution images at 20 respiratory phases over the breathing cycle. Global lung water density at functional residual capacity (minimum lung volume) was quantified with a user-independent machine learning lung segmentation approach. Additionally, the presence of patchy pathology was identified using an automated quantitative approach employing radiomic analysis of the lung parenchyma. We used a previously trained deep learning model to segment the lung parenchyma of our images (32). Once the parenchyma of each lung is isolated, intensities are discretized into 5% lung water density bins to simplify image features prior to feature extraction. Finally, 40 radiomic texture features are computed in three dimensions for each lung using a MATLAB (MathWorks, Natick, MA) toolkit (33).

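### Screening all serum and imaging parameters at p<0.2, then testing the survivors at an unadjusted 0.05 in the same patients, makes at least one false predictor of clinical outcome likely

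*Protocol article*

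**What the plan says.** The Statistical plan section of the protocol article sets out a two-step Cox analysis. The first step is wide: "Univariable Cox proportional regression of clinical outcome will be performed in all serum and imaging parameters". The second step takes forward what passes: "In the multivariable Cox proportional hazard analysis, all non-collinear parameters of interest with univariable" p below the threshold, and the sentence goes on, "0.2 will independently test for their association with composite outcome after adjustment for baseline risk". The significance rule is common to everything: a p "value less than 0.05 will be considered significant for all tests". The section gives no multiplicity control, no limit on how many parameters may enter, and no exploratory label for this analysis.

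On timing, the abstract says patients were "studied at 3–6 months following infection" and that "Clinical outcomes were collected up to 1 year from infection". Table 2 lists the clinical events as cardiovascular death or hospitalization and incident diabetes, dyslipidemia and hypertension. The composite outcome named in the Statistical plan is not defined there. No expected or observed event count is given, and the Sample size calculation section sets its target empirically, without reference to events.

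**The concern.** A p<0.2 screen lets about one in five unrelated parameters through. Testing the survivors at 0.05 in the same patients does not correct for that selection, and the p-values are reported as if each parameter had been the only one examined. With dozens of candidates, some will look like predictors by chance.

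The abstract gives the goal as finding treatment targets and ways to reduce cardiovascular risk after COVID-19. A marker that survives this procedure would be read as a lead for such a target, and the plan offers no way to tell a chance survivor from a real one. If the survivors are fitted together, the model may also hold more terms than the events can support, so the hazard ratios themselves could be unreliable.

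**Working it through.** The plan states no figure to reproduce for this analysis: neither an event target nor a number of events per variable. The check is therefore of the rule itself.

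**Inputs**
- Circulating parameters, from Tables 1 and 2 and the blood collection text: C-reactive protein, white cell count, d-dimer, troponin I, B-type natriuretic peptide, creatinine, electrolytes, AST, ALT, GGT, LDH, bilirubin, glucose, insulin, lipid profile = 15.
- MRI parameters, from Tables 1 and 2: lung water density, lung lesions, LVEF, myocardial T1 and T2, brain volume, brain lesions, susceptibility/iron, hepatic T1 and T2*, renal T1, muscle T1 and T2* (13), plus visceral, hepatic, intramuscular and intermuscular fat (4) = 17.
- Total K = 15 + 17 = 32. This is a minimum, since electrolytes, lipids and lung radiomics count once each. The lung imaging text says "40 radiomic texture features are computed in three dimensions for each lung"; if all were entered (an assumption), K = 32 − 1 + 80 = 111.
- N = 215 recovered patients. The outcome window is defined from infection, so it can apply only to them.
- Two-sided tests (assumed). Event rate not given; 5 to 20% at 12 months is assumed, about 11 to 43 events.

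**Expected false findings if all candidates are null**

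| | K = 32 | K = 111 |
|---|---|---|
| Pass the screen, 0.2K | 6.4 | 22.2 |
| Reach p<0.05, 0.05K | 1.6 | 5.6 |
| P(at least one), 1 − 0.95^K, if independent | 0.81 | 0.997 |

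**Simulation of the two-step rule**, N = 215, 32 null parameters, one real baseline-risk covariate, 12-month censoring, 250 runs per setting:

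| Event rate | Pairwise correlation | Pass screen | Events per variable, joint | P(≥1 false), joint | P(≥1 false), one at a time |
|---|---|---|---|---|---|
| 5% | 0 | 6.3 | 1.6 | 0.76 | 0.80 |
| 10% | 0 | 6.6 | 3.1 | 0.82 | 0.80 |
| 20% | 0 | 6.4 | 6.3 | 0.80 | 0.80 |
| 5% | 0.2 | 6.7 | 1.8 | 0.63 | 0.70 |
| 10% | 0.2 | 6.5 | 3.5 | 0.72 | 0.79 |
| 20% | 0.2 | 6.9 | 6.3 | 0.71 | 0.78 |

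Events per variable counts the baseline-risk term. A separate simulation at correlation 0.3 and event rates of 5/10/15% gave a joint chance of 50/58/52% and 1.4/2.8/4.1 events per variable. With 250 runs the Monte Carlo standard error is about 3 points. Across settings the chance is therefore roughly 50 to 80%. It falls as correlation rises and hardly moves with the event count.

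**Events needed for joint entry.** At a conventional 10 events per variable, about 6.5 survivors plus one baseline-risk term need 10 × 7.5 = 75 events, and 75/215 = 35% of patients within the window.

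**Follow-up after the visit.** Predictors come at 3 to 6 months and the window closes at 12, leaving 6 to 9 months. With constant hazard h = −ln(1 − rate)/12, events after a visit at v months number 215 × (exp(−hv) − exp(−12h)). This gives 5 to 8 of 11 events at 5%, 10 to 16 of 22 at 10%, and 20 to 31 of 43 at 20%.

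**Time origin.** With patients event-free at the visit, counting time from infection gave a single-marker type I error of 0.046 to 0.067, against 0.039 to 0.057 with delayed entry at the visit (1,500 runs per setting). The origin alone adds almost nothing. If events before the visit were counted and each shifted the marker by an assumed 0.5 SD, single-marker type I error was 13/15/22% at event rates of 5/10/20%; starting the clock at the visit brought it back to 4 to 6%.

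**The case against.** The best defence is that clinical events lie outside the primary outcomes, that the study looks for leads to be tested later, and that a condensed article may leave detail to an analysis plan. It is also fair that an all-null set is a worst case: glucose may well predict incident diabetes. And the wording about testing independently after adjustment for baseline risk can mean one marker at a time, which removes most of the overfitting.

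Part of this stands. It rules out saying that the analysis is bound to produce false predictors, and it makes the events-per-variable figures conditional on joint entry. It does not rescue the rule. The screen and the common 0.05 threshold are stated, not left open; the exploratory status is not stated for this analysis; and one-at-a-time testing still gave a 70 to 80% chance of at least one false finding.

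A reader might infer three stronger points that the article does not support:
- **Few events cause the false predictors.** No event count is given, a composite including incident hypertension and dyslipidemia could yield many events, and the false-positive chance barely depends on the count. Few events would chiefly make hazard ratios unstable.
- **Follow-up is counted from infection, so events before the scan reverse cause and effect.** The article gives a collection window, not the Cox time zero or a rule on earlier events.
- **Patients with existing hypertension (51), dyslipidemia (38) or diabetes (28) are counted as event-free for those components.** Table 2 says incident, and no text keeps prevalent cases in those risk sets.

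**Conclusion.** The concern holds for the screening rule. With at least 32 candidates, a p<0.2 screen followed by unadjusted 0.05 tests in the same 215 patients would, if all were null, pass about 6.4 and declare about 1.6 significant, with roughly a 50 to 80% chance of at least one false predictor. This rests on the count of listed items, two-sided tests and correlations of 0 to 0.3; it does not rest on the event rate or on joint versus single entry. Entering radiomic features separately would raise the candidate count and the expected number of false findings.

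Unstable hazard ratios are a second, conditional consequence: about 1.4 to 6 events per variable, if survivors are entered jointly and 5 to 20% of patients have an event. Time origin and prevalent disease are matters to pin down, not demonstrated errors. The point is worth acting on before the outcome analysis, which the article still describes in the future tense.

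**What to change.** - Delete the p<0.2 screen. Report every serum and imaging parameter as a single-marker hazard ratio adjusted for baseline risk, with false discovery rate control over the full list, and label the analysis exploratory. (A Bonferroni threshold would be 0.05/32 = 0.0016, holding the family-wise error at about 0.049 for independent tests; that is stricter than this purpose needs.)
- Limit any joint model to a baseline-risk score plus one or two markers fixed before the outcome analysis, with penalisation such as Firth's. Even three terms on 10 to 16 post-visit events (10% rate) give only about 3 to 5 events per term, so penalisation is needed.
- As safeguards, state that the Cox clock starts at the study visit, that only later events count, and that patients with a prevalent condition are left out of the risk set for that incident component. For the incident components this leaves 215 − 51 = 164 at risk for hypertension, 215 − 38 = 177 for dyslipidemia and 215 − 28 = 187 for diabetes. Define the composite in the same place.

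The cost is analysis wording. Fewer markers could be called independent predictors, and fewer events would count, since post-visit follow-up is 6 to 9 months. Extending chart review beyond the stated window is not required.
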